### Statistical methods

#### Sample size estimation

The sample size analysis is based on the *Z* test for fractions in two independent samples.

One of the purposes of this analysis is to compare fractions from two populations, with the hypothesis of their equality being tested. The *Z* test will be performed for two independent tests, with a type I error rate (α) of 0.01. The test is two-sided, so both positive and negative deviation from the hypothesis value can be considered significant. We assume that the population fractions in the groups are 0.50 and 0.05. In order to achieve 90.00% power, assuming that the sample numbers in the two groups are equal, a sample size of at least *N* = 27 from each group is required. For *N* = 27, the power in each group is 90.40%.

Assuming an optimistic scenario (no dropout interest and a sample of 80 people): Φ = Cramer’s *V* = 0.50396; relative benefit 10.0 [2.50–39.98].

The purpose of the effect size is to avoid a statistically significant result resulting only from a huge sample size, not from clinical effectiveness. Such a situation would not occur in the presented research. In conclusion, to show superiority of canrenone over placebo, a sample size of 80 patients was calculated based on the following assumptions: a two-tailed test, a type I error of 0.01, a power of 90%, efficacy of placebo of 5% (evaluated according to three trials testing vernakalant), efficacy of canrenone of 50% and a 20% dropout rate to fulfill the criteria of intention-to-treat analysis [12–14]. Due to a presumed low frequency of events, the secondary and safety endpoints will be evaluated in an exploratory manner.

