### Statistical analysis

Comparison of categorical variables (sinus rhythm restoration, AF recurrence, serious adverse reactions, safety outcome) between groups will be performed using the χ^2^ test of independence with Yate’s correction, or with Fisher’s exact test in cases of minimum expected count less than 5, and these will be expressed as number and percentage.

After initial assessment of the quantitative variables’ distributions (time to sinus rhythm restoration, SBP, DBP, HR), measures of location and dispersion will be calculated—as arithmetic mean and standard deviation for normally distributed variables, or as median and quartile range for variables for which the Shapiro–Wilk test null hypothesis has been rejected. For comparison of continuous variables between the two groups, the unpaired Student’s *t* test (or Cochran’s *C* test in the case of heteroscedasticity of variance) will be used, or for skewed data, the nonparametric Mann–Whitney *U* test. Differences for matched samples (within groups) will be evaluated with McNemar’s test, paired Student’s *t* test or Wilcoxon’s rank sum test.

All probability values will be calculated from two-sided tests, and *P* < 0.05 will be considered statistically significant. All statistical analysis will be performed using SAS 9.42 software (SAS Institute Inc.). After inclusion of 20 patients, effectivity and safety analyses will be performed by the statistician, Safety Committee and principal investigator, who will have access to interim results and will make the final decision to continue or terminate the trial. Hypotheses will be tested according to the significance level set to α ≤ 0.05 with 2-sided tests. Statistical analysis will be conducted using SAS 9.2 software.

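### The efficacy look at 20 of 80 patients can end the trial with no stated criterion and only an unadjusted 0.05 test level, although the sample size assumes one test at 0.01

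*Protocol article*

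**What the plan says.** Protocol article, Statistical analysis: "After inclusion of 20 patients, effectivity and safety analyses will be performed by the statistician, Safety Committee and principal investigator". These parties see the interim results and "will make the final decision to continue or terminate the trial". No threshold for benefit, futility or harm is given. The sentence that follows sets a two-sided 0.05 for hypothesis tests, and the same section earlier applies P < 0.05 to all probability values. Sinus rhythm restoration is to be compared by the Yates-corrected chi-square test, or by Fisher's exact test when the minimum expected count is below 5.

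Protocol article, Sample size estimation: the calculation uses a Z test "with a type I error rate (α) of 0.01", two-sided. The assumed rates are stated as "We assume that the population fractions in the groups are 0.50 and 0.05". The result is that "a sample size of at least *N* = 27 from each group is required", and the total of 80 is said to allow for 20% dropout. The calculation makes no allowance for a second look.

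**The concern.** Efficacy is examined at a quarter of the planned sample, and the result feeds a decision that may end the trial. The article does more than leave a boundary to another document. It states a level for every test, that level is not adjusted for two looks, and it is five times the alpha used for the sample size.

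Two things are at stake. First, if a favourable interim result may be declared a success, the trial has two chances to reject and the overall error may be larger than planned. Second, and without any alpha argument, a stop for benefit at 20 patients would rest on about 10 per arm. The effect estimate would be selected for being large, and safety would be informed by about 10 treated patients. The principal investigator shares the decision, so a rule fixed in advance matters more.

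**Working it through.** **Inputs.** Rates 0.50 and 0.05, two-sided alpha 0.01, power 90% and 27 per group come from Sample size estimation. The total of 80 comes from Study design, and 1:1 allocation from Randomization. The look at 20, the 0.05 level and the Yates/Fisher rule come from Statistical analysis. Assumptions: 10 per arm at the interim, 40 per arm at the end, and success declared if the interim p is at or below its level.

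**The plan's own figure.** With mean rate 0.275:

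n = [2.576·√(2·0.275·0.725) + 1.282·√(0.50·0.50 + 0.05·0.95)]² / 0.45² = (1.627 + 0.699)² / 0.2025 = 26.7, so 27.

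Power at 27 = Φ[(0.45·√27 − 1.627) / 0.545] = Φ(1.305) = 90.4%. Both figures reproduce, for one test at 0.01.

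**Type I error over two looks.** Normal theory: P(|Z1| ≥ c1 or |Z2| ≥ c2), with correlation √(20/80) = 0.5. Exact: P(p1 ≤ a1) + P(p1 > a1 and p2 ≤ a2), enumerated over all binomial outcomes with the planned Yates/Fisher rule, for common conversion rates up to 50%. To the digits shown, the exact maximum is the value at 50%.

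| Level at interim / final | Normal theory | Exact maximum | Final test alone, exact, at 50% rate | Exact at 5% common rate |
|---|---|---|---|---|
| 0.05 / 0.05 | 9.1% | 4.3% | 3.3% | 0.40% |
| 0.05 / 0.01 | 5.7% | 1.7% | 0.49% | 0.03% |
| 0.01 / 0.01 | 1.9% | 0.73% | 0.49% | 0.02% |
| 0.001 / 0.01 | 1.08% | 0.51% | 0.49% | 0.02% |

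In the first row the look adds 4.33 − 3.30 = 1.03 points; the rest is the final test at 0.05. In the second row it adds 1.70 − 0.49 = 1.21 points, and that alone takes the total past 1%. At 0.05 / 0.05 the exact error passes 1% at a common rate of about 8%. At 0.05 / 0.01 it is 1.10% at a rate of 20% and 1.60% at 30%.

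**Chance of crossing p ≤ 0.05 at 10 per arm under 50% versus 5%.** With 0, 1, 2 or 3 placebo conversions, canrenone needs at least 5, 7, 8 or 9:

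0.5987·0.6230 + 0.3151·0.1719 + 0.0746·0.0547 + 0.0105·0.0107 = 0.3730 + 0.0542 + 0.0041 + 0.0001 = 0.431.

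The mean observed difference over these outcomes is 60 points, against a true 45. Under 30% versus 5% it is 54 points against a true 25, but crossing then happens only 9% of the time. The smallest crossing result, 5/10 versus 0/10, has p = 0.033 and a Newcombe 95% interval of about 12 to 76 points.

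**Chance of crossing p < 0.001 under 50% versus 5%.** This needs at least 8/10 versus 0/10, or 10/10 versus 1/10 or 2/10:

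0.5987·0.0547 + (0.3151 + 0.0746)/1024 = 0.0327 + 0.0004 = 0.033.

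**The case against.** A reader might infer that the interim look in itself pushes the error above 0.01. The documents do not support that, for four reasons.

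- **Source of the excess.** Most of it at 0.05 / 0.05 comes from analysing at 0.05 a trial sized at 0.01. The final test alone reaches 3.3%.
- **It is not unconditional.** The planned tests are conservative. At 0.01 for both looks the exact error never exceeds 0.73%. At the plan's assumed placebo rate of 5% it is 0.40% even with 0.05 at both looks. The worst case of 4.3% is still below the 0.05 that Statistical analysis declares. The 9.1% belongs to the Z test under normal theory, whereas that section names Yates/Fisher for this endpoint.
- **It needs an efficacy claim.** The text says continue or terminate, without saying on what ground. Stopping for harm or futility adds no type I error.
- **Other documents.** A full protocol or analysis plan not shown may hold a boundary, so the fair wording is that none is stated here.

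These points limit the size of the claim and stand. They do not remove it. The article puts 0.05, not 0.01, beside the interim look. The 5% placebo rate is borrowed from vernakalant trials, and the error rate must hold at whatever the true rate is. Efficacy is named as an input to the decision, and stopping for benefit is not excluded. The pilot label lowers the stakes, but the sample size section still aims to show superiority.

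**Conclusion.** The point holds as a conditional one. The article plans an efficacy look at 20 of 80 patients with authority to terminate and no stated criterion. The only test level it gives is an unadjusted two-sided 0.05, against a single-test 0.01 for the sample size. If the look can end in an efficacy claim, the exact type I error can reach 4.3% at 0.05 / 0.05, about one point of it due to the look, or 1.7% at 0.05 / 0.01. It stays below 1% if 0.01 applies at both looks.

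The early-stopping problem does not depend on which alpha was meant for the final test. If the design rates are right, there is a 43% chance that about 10 per arm reach the stated level, with an observed effect some 15 points too large on average.

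These figures assume equal arms at each look. No blocking is stated, so 10 per arm is approximate.

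**What to change.** State one alpha for the primary test, 0.01 to match the sample size, and remove the conflicting 0.05 for that test. Without this step the main source of excess stays: p < 0.001 at the interim followed by 0.05 at the end would still allow 3.3%.

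Then choose one of two options:

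- make the 20-patient look safety-only, with no between-arm efficacy test; or
- prespecify an efficacy boundary of two-sided p < 0.001 at the interim with the final test at 0.01, and state that no other interim result permits stopping for benefit. The exact maximum error is 0.51%. Normal theory gives 1.08%, marginally above 1%.

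This takes two or three sentences and no extra patients. The cost is a smaller chance of stopping very early for benefit. With the boundary, the chance of crossing at 20 patients under the design rates falls from 43% to about 3%; with a safety-only look it is nil.

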**Fig. 1 Fig1:**
[figure not shown]
Schedule of enrolment, interventions and assessments. AF atrial fibrillation, ECG electrocardiogram

Patients admitted to the Emergency department at the National Institute of Cardiology and diagnosis of a new onset atrial fibrillation are considered for participating in the study. Strategies for achieving adequate participant enrollment to reach the target sample size include graphic advertisements, periodical meetings with staff and repeated mailing actions.

All patients included in the trial, whether allocated to the study or control group, are managed in the same way according to protocols of pharmacological cardioversion. Such protocols are not specified by the trial, but they include standard components, comprising clinical evaluation, plasma electrolyte level assessment, baseline 12-lead ECG performance, continuous ECG monitoring, periodic noninvasive blood pressure (BP) control and an intravenous line.

Rate control medications, such as β-blockers or calcium channel blockers (diltiazem, verapamil), are allowed in the previous 2 h before study intervention. Chronic antiarrhythmic therapy is not an exclusion criterion—an AF episode indicates its low efficacy.

The assumptions of the study are explained to the patient and informed written consent is obtained. A case report form (CRF) is created for each patient. Investigators collect data regarding medical history, demographics, clinical presentation, previous and current treatment, and diagnostic test results. Both substances are prepared earlier in syringes by the study nurse unblinded to patient assignment. The study drug or placebo is administered intravenously in boluses by a nurse under the supervision of the enrolling physician, both blinded to patient assignment. In the case of serious adverse event occurrence, unblinding by the principal investigator is permissible, who will start the procedure for revealing a participant’s allocated intervention during the trial***.***

Each patient is observed within 2 h after the last bolus supply in order to determine efficacy and adverse reactions. The maximum concentration of canrenone is achieved within the first hour and decreases in two phases, with a mean half-life of 5–14 h, respectively [10].

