### Randomization

Randomization is provided by the independent statistician using SAS software (SAS Institute Inc., Cary, NC, USA). After eligible patients provide informed consent, they are assigned a specific identifier. Neither the patient nor the researcher knows which group the subject will be assigned to. Patients are randomized according to the implemented random allocation sequence using numbered sealed envelopes, which are opened after inclusion of the patient for the study in a 1:1 ratio to treatment with canrenone or placebo.

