#### Endpoints

The primary endpoint is sinus rhythm restoration documented in the ECG within 2 h after canrenone supply.

Secondary endpoints are the following:
Time to sinus rhythm restorationAF recurrence within the observation periodSerious adverse reactions, which refer to every event requiring admission to a hospital or extended observationSafety outcomes (exploratory analysis):
Hypotension < 90 mmHgCardiac conduction abnormalitiesNew arrhythmia occurrence

Data relating to the primary endpoint will be validated by a Clinical Committee. Data relating to safety will be monitored by a Safety Committee composed of three cardiologists with academic degrees experienced in conducting clinical trials. All adverse events are reported every month to the Safety Committee and the local ethics committee. These processes will be independent from investigators and the sponsor.

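### The principal investigator sees the interim results and shares the stopping decision, against the stated independence of safety monitoring and with 60 of 80 patients still to be enrolled

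*Protocol article*

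**What the plan says.** All references are to the protocol article.

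- **Statistical analysis**, on who does the interim work: "After inclusion of 20 patients, effectivity and safety analyses will be performed by the statistician, Safety Committee and principal investigator". The same sentence ends with the "principal investigator, who will have access to interim results and will make the final decision to continue or terminate the trial". Grammatically, the last clause may refer to all three parties or to the principal investigator alone. On either reading the principal investigator sees the results and takes part in the decision.
- **Endpoints**, on oversight: "Data relating to safety will be monitored by a Safety Committee composed of three cardiologists". The paragraph also covers validation of the primary endpoint by a Clinical Committee and monthly reporting of adverse events. It closes: "These processes will be independent from investigators and the sponsor".
- **Study procedures**, on the blind: the drug is given "by a nurse under the supervision of the enrolling physician, both blinded to patient assignment". The one unblinding route given to the principal investigator is a serious adverse event: "In the case of serious adverse event occurrence, unblinding by the principal investigator is permissible".
- **Study design**: one institute, 80 patients, double-blind.

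No section limits the principal investigator to pooled or masked interim data.

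**The concern.** One section promises that safety oversight is kept apart from the investigators. Another puts the lead investigator among those who analyse the interim safety data, hold the results and decide what follows. An analysis plan that is not shown could add detail, but it could not make both statements true as written.

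The efficacy half of the look raises a separate issue. Someone who runs a double-blind trial and knows how the arms compare at 25% of enrolment can be influenced by it. Two things are then exposed:

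- **The stopping decision.** It is shared by a person with a stake in the trial, rather than made on the advice of people outside it.
- **Trial-level masking.** The emerging effect can colour later conduct. Entry depends partly on the attending physician's judgement that the patient is cardiopulmonarily stable. Whether an event counts as serious can turn on whether observation was prolonged.

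**Working it through.** **1. The texts side by side**

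| Activity | Endpoints section | Statistical analysis section | Result |
|---|---|---|---|
| Safety review | Safety Committee, independent of investigators and sponsor | Interim safety analysis by statistician, Safety Committee and principal investigator | Direct conflict |
| Primary endpoint | Validated by a Clinical Committee, independent of investigators and sponsor | Interim effectiveness analysis by the same three parties | Not a literal conflict: validating an endpoint is not analysing it. The tension is with the double-blind design |
| Decision to continue | Not addressed | Includes the principal investigator | The safety input to this decision is not independent |

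**2. How much of the trial follows the look**

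Inputs: 20 patients at the look (Statistical analysis) and 80 in total (Study design).

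- Fraction enrolled: 20/80 = 25%.
- Still to be enrolled: (80 − 20)/80 = 60/80 = 75%.

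**3. Would coded arms protect the masking?**

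The plan's own rates are 0.50 on canrenone and 0.05 on placebo (Sample size estimation). To confirm they are read as the plan uses them, its figure is reproduced with two-sided α = 0.01, 90% power and mean rate 0.275:

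- n per group = [2.5758·√(2·0.275·0.725) + 1.2816·√(0.5·0.5 + 0.05·0.95)]² / 0.45² = (1.6266 + 0.6990)² / 0.2025 = 26.7, so 27.
- Power at 27 = Φ[(0.45·√27 − 1.6266)/0.5454] = Φ(1.305) = 0.904.

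Both agree with the plan's 27 per group and 90.40%.

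With 1:1 allocation, 20 patients give about 10 per arm. Expected conversions are 10 × 0.50 = 5 on canrenone and 10 × 0.05 = 0.5 on placebo. If the plan's assumptions are near the truth, arms labelled only A and B would probably identify themselves. With a much smaller true effect they would be less revealing.

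**4. Has the look probably taken place?**

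The document does not give actual accrual, so this rests on an assumption. The Trial status section plans recruitment from January 1, 2019 to December 31, 2021, which is 36 months.

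- Even accrual: 80/36 = 2.2 patients a month, so patient 20 arrives at 20/80 × 36 = 9 months.
- The article appeared on 12 May 2020, about 16.4 months after the start. The look falls before that date if accrual averaged more than 20/16.4 = 1.2 a month, about 55% of the planned rate. It falls later if accrual was slower.

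**5. Size of any bias**

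The document contains nothing from which the bias could be computed, so no figure is offered.

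**The case against.** The strongest reply is that the blind on individual patients is untouched. Totals by arm for the first 20 patients say nothing about which treatment any of the next 60 will receive. An unblinded study nurse prepares the syringes, the administering nurse and enrolling physician are blinded, and allocation is by sealed envelope. If staff do not know the allocation, a shift in selection or reporting would tend to affect both arms alike. This stands, and it limits the harm to trial-level masking and the decision itself.

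Four stronger readings are tempting, and the document does not support them:

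- **That the blind is broken.** The text gives access to interim results, not to allocation codes. Results by arm are inferred from the purpose of the look.
- **That the Randomization section is contradicted.** It states: "Neither the patient nor the researcher knows which group the subject will be assigned to". That concerns each patient's assignment, and knowledge of aggregate results is compatible with it.
- **That co-treatment inside the 2-hour window is opened to bias.** Study procedures places further treatment after that window or after sinus rhythm returns. Before that point, only rescue medication in case of need is mentioned.
- **That the principal investigator decides alone, or runs enrolment and assessment.** The most natural reading is a shared decision, and enrolment is assigned to the enrolling physician. Influence over the team is plausible at a single centre but is not stated.

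It can also be said that the independence sentence describes routine monitoring and not the one-off interim analysis. That carries weight for efficacy. It is weak for safety: an interim safety review in which the Safety Committee takes part is hard to separate from the safety monitoring that the sentence covers.

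Finally, this is a pilot with an ECG-documented endpoint validated by a committee independent of the investigators. That protects endpoint classification. It does not make the stopping decision independent.

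**Conclusion.** The concern holds in a limited form. For the interim safety review, the Statistical analysis and Endpoints sections conflict and must be reconciled. For efficacy, the principal investigator of a single-centre double-blind trial would know the emerging effect and share the decision to continue after 25% of planned enrolment, with 60 patients still to come.

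The efficacy part rests on one inference, that an effectiveness judgement in a two-arm superiority trial uses results by arm. The document describes no masking that would point the other way.

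What is at risk is the independence of the stopping decision and trial-level masking, for example in the selection of later patients. Individual allocation and classification of the ECG endpoint remain protected. The direction and size of any bias are unknown.

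**What to change.** Amend the Statistical analysis section so that:

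- interim results by arm go only to the existing three-member Safety Committee and to a statistician not involved in trial conduct;
- the committee issues only a recommendation to continue, modify or stop;
- the principal investigator receives that recommendation and does not see interim results.

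This brings the section into line with the independence stated under Endpoints.

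**Cost.** Sample size and trial procedures do not change. The committee already exists, and the Randomization section already mentions an independent statistician. The document does not say whether that person is separate from the biostatistician responsible for the database, so this should be confirmed. Under Study design, the modification has to be reported to the regulator, the registry and the ethics committee.

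**If the look has already taken place**, rewording cannot restore the masking. The trial report should then state who saw which results and when, and how the decision to continue was reached.

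### The trial is sized, and its primary test described, at a two-sided type I error of 0.01, but the analysis section judges every test at 0.05, and nothing reconciles the two

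*Protocol article*

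**What the plan says.** Protocol article, *Sample size estimation*. The Z test "will be performed for two independent tests, with a type I error rate (α) of 0.01". The section adds that "The test is two-sided, so both positive and negative deviation from the hypothesis value can be considered significant". On that basis it derives 27 per group, with a stated power of 90.40%, for conversion rates of 0.50 and 0.05. The closing summary gives the basis for 80 patients as "a two-tailed test, a type I error of 0.01", together with 90% power and 20% dropout.

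Protocol article, *Statistical analysis*. Sinus rhythm restoration, the primary endpoint, is listed among the categorical variables. It is to be compared with a Yates-corrected chi-square test, or Fisher's exact test when the smallest expected count is below 5. The section then sets the threshold twice: P "< 0.05 will be considered statistically significant", and later "Hypotheses will be tested according to the significance level set to α ≤ 0.05 with 2-sided tests". Neither sentence makes an exception for the primary endpoint.

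Both sections are two-sided. Only the level differs. Nothing in the article limits 0.01 to the sample size calculation, or 0.05 to the secondary and safety endpoints.

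**The concern.** The level at which the primary test counts as positive is a core part of pre-specification, and here it has two values. A result with P between 0.01 and 0.05 would be a success by the analysis section and a failure by the type I error on which the trial was sized. Whoever reports the trial could cite either section after seeing the data. The published power figure also belongs to a stricter decision rule than the one the analysis section applies.

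Timing adds to this. *Statistical analysis* gives the statistician, the Safety Committee and the principal investigator interim effectiveness results after 20 patients. A choice of level made after that look would be less credible than one made before it.

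**Working it through.** **Inputs.** From *Sample size estimation*: rates 0.50 and 0.05, two-sided test, 90% power, equal groups, 80 patients, 20% dropout. From *Statistical analysis*: the Yates or Fisher rule and the 0.05 threshold. With no dropout there are 40 per arm; with 20% dropout, 80 × 0.8 = 64, or 32 per arm. True canrenone rates of 25% and 30% are my assumptions, used to show a range.

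**1. Reproduce the plan's figure.** Pooled Z test without continuity correction:

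n per group = [z(1−α/2)·√(2·p̄·(1−p̄)) + z(0.90)·√(p₁(1−p₁) + p₂(1−p₂))]² / (p₁ − p₂)²

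Here p̄ = 0.275, √(2 × 0.275 × 0.725) = 0.6315, √(0.25 + 0.0475) = 0.5454, and the difference squared is 0.45² = 0.2025.

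- α = 0.01: (2.576 × 0.6315 + 1.282 × 0.5454)² / 0.2025 = 26.7, so **27**. Power at 27 is **90.40%**. Both match the article.
- α = 0.05: (1.960 × 0.6315 + 1.282 × 0.5454)² / 0.2025 = 18.5, so **19**. Power at 27 would be **97.8%**.

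So 0.01 was really used in the calculation and is not a misprint.

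**2. Results that change verdict.** At 40 per arm with 2/40 on placebo, the smallest expected count is at least 6 in each case below, so the Yates test applies: χ² = N(|ad − bc| − N/2)² / (product of the four margins).

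| Canrenone vs placebo | χ² (Yates) | P | At 0.05 | At 0.01 |
|---|---|---|---|---|
| 10/40 vs 2/40 | 80 × 280² / (40 × 40 × 12 × 68) = 4.80 | 0.028 | positive | negative |
| 11/40 vs 2/40 | 80 × 320² / (40 × 40 × 13 × 67) = 5.88 | 0.015 | positive | negative |
| 12/40 vs 2/40 | 80 × 360² / (40 × 40 × 14 × 66) = 7.01 | 0.008 | positive | positive |

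**3. How often the two sections would disagree.** Full enumeration of two binomials with the Yates or Fisher rule, giving the probability of 0.01 ≤ P < 0.05:

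| True rates | 40 per arm | 32 per arm |
|---|---|---|
| 50% vs 5% (protocol) | 1.4% | 4.7% |
| 30% vs 5% (assumed) | 21.6% | 28.0% |
| 25% vs 5% (assumed) | 23.7% | 26.1% |

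**4. Power of the planned Yates or Fisher test at 50% vs 5%.** At 0.01 it is 98.4% with 40 per arm and 94.1% with 32. At 0.05 it is 99.7% and 98.8%.

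**5. Actual type I error.** Enumerated over common rates from 0.01 to 0.50 at 40 per arm, the worst-case size is 3.3% at nominal 0.05 and 0.5% at nominal 0.01.

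**The case against.** The strongest reply is that the analysis section governs. It names the primary endpoint, its test and a threshold of 0.05, while 0.01 appears only in the sizing section. Sizing at a stricter level than the test will use is legitimate conservatism. The sizing section also refers to a Z test that the analysis section does not use, so its wording is weak evidence of a 0.01 decision rule.

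Part of this stands. The sizing text already differs from the planned analysis in its choice of test, and conservative sizing is permissible. But the article never calls 0.01 a margin. It words 0.01 as the level at which the test will be performed and again as the type I error behind the 80 patients. A reader cannot tell conservatism from contradiction.

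It is also fair that the practical effect is small if the design assumption is right. The larger split probabilities need canrenone rates of 25–30%, which the article does not contain.

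Two stronger readings are tempting and do not hold. A reader might infer that the false-positive rate becomes five times the design value. That ratio is nominal only: the planned test is conservative, and its worst-case size at nominal 0.05 stays below 5%. A reader might also fault the 0.05 convention for the secondary and safety endpoints. These are already labelled exploratory, and a descriptive P value does not contradict that label.

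**Conclusion.** The contradiction is real and concerns the primary decision threshold. The sample size and the power statement reproduce only at two-sided 0.01, while the analysis section twice applies 0.05 to all tests. Outcomes of 10/40 or 11/40 against 2/40 would be reported differently depending on the section followed.

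Its practical reach depends on the true effect: slight at the protocol's own rates, and about one trial in four or five at 40 per arm if canrenone converts 25–30%. All these figures assume equal arms and the planned Yates or Fisher rule.

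A reader might infer that the trial is underpowered or has to be resized. It does not: on the stated rates, 80 patients give more than 90% power at either level, including after 20% dropout. Nor does the article say which level was intended, so 0.01 is a recommendation from the design basis and not a reading of the text.

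**What to change.** Before any unblinded look, including the one after 20 patients, name one two-sided level for the primary endpoint. State it identically in *Sample size estimation* and *Statistical analysis*, and say that 0.05 otherwise applies only to exploratory comparisons.

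- **If 0.01 (the natural choice):** the 27 per group and 90.40% stand as written, because they rest on that level. The cost is a higher bar: against 2/40 on placebo, success needs 12/40 instead of 10/40. Power with the planned test is about 98% at 40 per arm and 94% at 32 per arm after 20% dropout, under 50% versus 5%.
- **If 0.05 was intended:** restate the sample size basis and power at that level. By the protocol's formula, 19 per group gives 90% power, and power is 97.8% at 27 per group.

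Either way the change is wording only. It needs no extra patients, procedures or data.
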